### Ethical aspects

The study protocol, its updates and all the questionnaires have been submitted for approval by the Regional Ethics Committee. The study uses a convenience sample, *i.e.*, the participants have volunteered. Participation in the study is based on informed consent. In addition, an extensive Risk Assessment Report has been produced to identify potential risks and appropriate practices have been adopted to minimize the identified risks. For example all data will be gathered and stored in de-identified form and user-related data will be secured through necessary encryption and authentication.

## Design

Skibotn Rehabilitation Centre receives each month (except from July) a group of 10–20 CVD patients that are admitted in the rehabilitation programme. Since these people are hosted in the same environment for all of this period and social interaction related to the rehabilitation is encouraged, a randomisation among the members of the same group would make it very likely for patients to realize whether they belong to the control or intervention branch. In order to minimize this risk of contamination of the control group, the participants will be blinded to condition by randomizing the monthly clusters of participants to one of two conditions:

(1) A control condition involving a basic Internet-based self-management intervention

(2) An experimental condition where the participants get access to a tailored and enhanced version of the Internet-based intervention

The researchers are also blinded for the condition of each monthly group, so we will avoid introducing any bias in the analysis of the data. To ensure true randomness of the groups, we used random.org to allocate the groups to the two conditions. Random.org is a true random number online service that is based on the atmospheric noise. The duration of the study is one year after the discharge from the cardiac rehabilitation programme.

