#### Sample size estimation

Power analysis for *a priori* sample size estimation was performed with equivalence test for two-proportions in a cluster-randomized design by the computer program PASS [28]. The participants that attend the cardiac rehabilitation programme together a given month, consist a cluster. Based on previous research with chronic disease self-management [29] it is reasonable to expect that the proportions meeting goals for all self-management behaviours at one-year follow-up will be relatively low *e.g.*, 15% *vs.* 5%. To discover differences of this size between two groups at a 0.05 alpha level and with 0.80 power, we need a total sample of 16 clusters with 15 participants each. We will recruit a total of 17 clusters, equalling continuous recruitment of all the participants of the cardiac rehabilitation programme of Skibotn Centre over 18 months.

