### Procedure

During the first days of the stay of each monthly group at the Centre, a physiotherapist, who is member of the staff there and administrator of the site, presents the website and the study, answers questions and distributes the consent form to the participants that are interested. Then another session is scheduled for those participants that decide to sign the consent form and take part in the study. In this additional session, the participants are registering to the website, fill-in online the baseline questionnaire and they receive training on how to use the website. During these two meetings the potential participants are generally informed of the features of the site and of the two study conditions, but not in such detail that it will be possible for them to understand in which group they belong.

At the end of the rehabilitation stay, participants are offered a repetition Internet-training session, and are being asked to log-on to fill out the Post-rehab questionnaire. The participants are being encouraged to keep visiting the intervention website after they return home, and are given prompts by email and SMS (Short message service) to fill out follow-up questionnaires at 1, 3, and 12 months after leaving the centre.

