### Statistical analysis

As participants are randomized at group level, a multilevel analysis will be performed to check for clustering effects. If the intraclass correlation coefficients for our primary outcome variables are different from zero this will be taken into account in the following analyses, in order to reduce p-value bias. Potential confounders will be added as covariates. Data analysis will be performed using IBM SPSS and MLWiN. Group differences after intervention will be analysed with baseline data as a covariate in ANCOVA. Should clustering effects be found, multilevel mixed regression will be used.

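### Calendar months are the randomised units, but no season control is stated in allocation or analysis, and the ordinary ANCOVA fallback would ignore a chance seasonal imbalance at 1 and 3 months

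*Protocol article*

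**What the plan says.** The Sample size estimation section defines the cluster: "The participants that attend the cardiac rehabilitation programme together a given month, consist a cluster". The Design section randomises those clusters and gives the reason, contamination between people staying together: "the participants will be blinded to condition by randomizing the monthly clusters of participants to one of two conditions". The allocation method is described in one place: "To ensure true randomness of the groups, we used random.org to allocate the groups to the two conditions". No blocking, pairing or stratification is mentioned, and the draw is not called simple or unrestricted either.

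On numbers, "We will recruit a total of 17 clusters, equalling continuous recruitment of all the participants of the cardiac rehabilitation programme" over 18 months, with no July group (Design).

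Under Procedure, baseline is completed early in the stay, and participants are prompted "to fill out follow-up questionnaires at 1, 3, and 12 months after leaving the centre". The stay lasts four weeks (Participants). The main outcome is self-reported physical activity (Measures), assessed at all three follow-up times (Abstract).

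The Statistical analysis section says: "Group differences after intervention will be analysed with baseline data as a covariate in ANCOVA". It adds unnamed potential confounders as covariates and moves to multilevel mixed regression only if clustering effects are found. Neither season nor calendar month appears anywhere in the article.

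**The concern.** Because the randomised unit is a month, all members of a cluster reach each follow-up in the same part of the year. Anything that changes self-reported activity with the season therefore acts between clusters and never within them. Seventeen units are too few for chance to balance such a factor reliably. A good source of random numbers makes the draw fair but does not make it balanced.

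The planned safeguards do not clearly reach this. The baseline covariate is measured in a different season from the 1- and 3-month outcomes. The cluster-level model depends on what the data show about clustering, and with 17 clusters modest clustering is easily missed. If it is missed, an excess of winter follow-up in one arm enters an ordinary ANCOVA as if the participants were independent. It can then pass for an effect of tailoring or hide one.

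**Working it through.** **Inputs from the article.** 17 monthly clusters in 18 months, no July group, 15 participants per cluster, a four-week stay, follow-up at 1, 3 and 12 months after leaving, and a planned difference of 15% vs 5%.

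**Assumptions, not in the article.** Winter follow-up means November to April. The seasonal effect is a cosine curve over the year with a peak-to-trough range of 0.2, 0.3 or 0.5 SD of activity. There is no other clustering.

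**1. Calendar.** Eighteen consecutive months give 17 groups only if they contain one July, so entry starts in January or in August to December. Follow-up falls about 1+1 = 2, 1+3 = 4 and 1+12 = 13 months after baseline. Over these starts and lags, between 5 and 12 of the 17 clusters have winter follow-up.

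**2. Chance imbalance in the share with winter follow-up.** For K winter clusters and a fixed 8:9 split, with p = K/17, SD = √[p(1−p) × 17/16 × (1/8 + 1/9)]. With K = 9 this is √(0.529 × 0.471 × 1.0625 × 0.236) = 0.25. Simulation over the six starts and three lags gives:

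| Allocation | Arms differ by ≥25 points | Arms differ by ≥40 points |
|---|---|---|
| Simple draw | 31–36% | 9–15% |
| Fixed 8:9 | 29–35% | 3–16% |
| Months paired by season | 0% | 0% |

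The risk hardly depends on whether the arm sizes were fixed.

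**3. Size of the shift.** If the proportion meeting goals differed between winter and summer by an assumed 5, 10 or 20 points, a 25-point imbalance would move the arm contrast by 0.25 × 5 = 1.25, 0.25 × 10 = 2.5 or 0.25 × 20 = 5 points, against the planned 10.

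**4. What baseline adjustment can do.** The correlation across the 17 months between a winter-peaked term at baseline and at follow-up is about 0.4 to 0.5 for the 1-month outcome, about −0.4 to −0.5 for the 3-month outcome and about 0.85 for the 12-month outcome. Baseline therefore absorbs part of season at 12 months and little at 1 month. At 3 months it points the other way.

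**5. False positives under ordinary ANCOVA.** With amplitude A equal to half the range, the between-cluster variance is v = A² × 0.5, ICC = v/(1+v), and the design effect is DE = 1 + 14 × ICC. The actual two-sided error at a nominal 5% is 2[1 − Φ(1.96/√DE)].

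| Range (SD) | v | ICC | DE | False-positive rate |
|---|---|---|---|---|
| 0.2 | 0.005 | 0.005 | 1.07 | 5.8% |
| 0.3 | 0.011 | 0.011 | 1.16 | 6.8% |
| 0.5 | 0.031 | 0.030 | 1.42 | 10.1% |

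Simulation without the baseline covariate agrees: about 6%, 7% and 10–11%. A half-year or dark/light term lowers these to about 5–7%. The cluster-level test stays at 5% throughout.

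**6. Would clustering be found?** A 5% F test across 17 clusters of 15 has noncentrality 15 × 17 × v = 1.3, 2.9 and 8.0. Its chance of detecting the seasonal clustering is then about 8%, 13% and 33%. The article does not say what rule decides that an ICC differs from zero.

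**7. Price of one season term if season has no effect.** Degrees of freedom fall from 15 to 14, so t rises from 2.131 to 2.145. Chance correlation between arm and season costs about √(16/15). Together, 2.145/2.131 × 1.033 = 1.04.

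**The case against.** The strongest reply is that random allocation makes seasonal imbalance chance, not bias. That is right. Season adds between-cluster variance, and a cluster-level analysis carries it in its standard error. What stands against the plan is only that this analysis is conditional.

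A second reply is that a condensed article need not list every restriction or covariate, and that its potential confounders may include season. That also has force. Season adjustment is not excluded, only unnamed, and the background variables under Measures need not be a closed list. A reader might infer that the draw was unrestricted. The article does not say so: it names a number source, from which a blocked or fixed-count list can equally be drawn. The point does not need that inference, because a fixed 8:9 split leaves nearly the same seasonal imbalance.

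A third reply concerns 12 months, the time on which the sample size rests. A reader might infer that baseline adjustment is useless. At about 13 months after baseline the season is nearly the same, so part of the imbalance is absorbed. The argument is strong only at 1 and 3 months.

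Finally, the size of any seasonal effect is assumed. At 0.2 to 0.3 SD the excess error is only one to two percentage points.

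**Conclusion.** The point holds as a limited one. Months are the randomised units, no season control is stated, and a marked seasonal imbalance between the arms is likely enough (about one draw in three at 25 points or more) to be worth planning for. Baseline adjustment does not remove it at 1 and 3 months.

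The harm comes through the ordinary ANCOVA fallback, whose false-positive rate would be about 6%, 7% or 10–11% at assumed seasonal ranges of 0.2, 0.3 or 0.5 SD. These rates assume no other clustering and apply if ANCOVA is used whatever the data show. The article supplies no seasonal effect, so they show sensitivity and are not estimates. The documents do not support a claim that the trial is biased by season or that its randomisation was faulty.

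**What to change.** In the Statistical analysis section, before unblinding:

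- Name one season-of-follow-up term, a half-year or dark/light indicator derived from the follow-up month, as a covariate in the arm comparison, chiefly for the 1- and 3-month outcomes.
- Fit the cluster-level model regardless of the observed ICC.
- State any restriction that was placed on the allocation.

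No new data are needed, because follow-up month is fixed by discharge month. The season term costs one of about 15 cluster degrees of freedom and makes intervals about 3–4% wider if season has no effect. A larger set of calendar terms is not advised: at assumed ranges of 0.2 to 0.3 SD, sine, cosine and cluster-sequence terms together widen the interval.

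The article describes the allocation in the past tense, and an allocation already made should not be redone. Blocking by calendar time is an option only if some months are still unallocated. It would make the next month's condition easier to guess, which matters because centre staff present the study to each group after it arrives.

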### Control internet-based intervention

All participants will be given access to a basic Internet-based intervention, “ikkegideg.no” (Norwegian for “Don’t give up”), consisting of general information about CVD and self-management, including diet, physical activity, smoking and medication, and a discussion forum. In the discussion forum we have two levels of accessibility. There is the closed groups level, where the users are able to create and take part in discussions that are only accessible by those that are members in the same monthly group. Users that belong to the same monthly group have met physically during the rehabilitation programme and it is expected that the level of trust among them will be higher. At the same time, all the users will be able to create, read and take part in discussions that will be visible by all the registered users of the website. This helps the discussion forum to become more active, since more users will be contributing to the discussions.

### Enhanced internet-based intervention

In the intervention group, the participants will in addition to general information and the discussion forum have access to the following: (1) content tailored to stage of change, regulatory focus and self-efficacy; (2) behavioural monitoring (self-reported physical activity).

The tailoring process is in some ways emulating face-to-face patient counselling. The answers that patient gives to the questionnaires creates an individualized path through the intervention, including feedback and follow-up questions based on predefined algorithms. Different answers to the same questions over the time generate changes in the treatment or behaviour change plan that reflect the changes in a patient’s characteristics or change process [14]. The adaptive tailoring in this intervention is based on integrative models that combine socio-cognitive determinants of health behaviour with a process view, such as the Integrated Model for explaining motivational and behavioural change I-Change [30] and the Health Action Process Approach HAPA [25]. Thus, we tailor to stage of change [24], which determine when the other concepts are tailored on; for instance, self-efficacies [25,29,31], and regulatory focus [26,32].

### Procedure

During the first days of the stay of each monthly group at the Centre, a physiotherapist, who is member of the staff there and administrator of the site, presents the website and the study, answers questions and distributes the consent form to the participants that are interested. Then another session is scheduled for those participants that decide to sign the consent form and take part in the study. In this additional session, the participants are registering to the website, fill-in online the baseline questionnaire and they receive training on how to use the website. During these two meetings the potential participants are generally informed of the features of the site and of the two study conditions, but not in such detail that it will be possible for them to understand in which group they belong.

At the end of the rehabilitation stay, participants are offered a repetition Internet-training session, and are being asked to log-on to fill out the Post-rehab questionnaire. The participants are being encouraged to keep visiting the intervention website after they return home, and are given prompts by email and SMS (Short message service) to fill out follow-up questionnaires at 1, 3, and 12 months after leaving the centre.

### Measures

For an overview of all measures over the different measurement time points, please see Table 1.

**Table 1 T1:** Overview of measures over the different time points of the study

	**Baseline**	**Post-rehab**	**1 month**	**3 months**	**12 months**
Socio-economic status	Y				
Co-morbidity	Y				Y
Alcohol use	Y				Y
Health-related Internet use	Y				Y
Disease related symptoms	Y	Y	Y	Y	Y
iPAQ	Y	Y	Y	Y	Y
Social support	Y	Y	Y	Y	Y
Self-efficacies	Y	Y	Y	Y	Y
HADS	Y	Y	Y	Y	Y
Perceived Tailoring			Y	Y	Y
Stage of change	Y	Y	Y	Y	Y
Decisional balance	Y	Y	Y	Y	Y
Regulatory focus	Y				
7-day smoking abstinence	Y	Y	Y	Y	Y
Quality of life	Y	Y	Y	Y	Y
Usage logging	Y	Y	Y	Y	Y
User evaluation			Y		Y
Return to work	Y		Y	Y	Y

The main outcome for this study is maintenance of physical activity, measured through self-report. Secondary outcomes are self-efficacy, perceived social support and user evaluation of the intervention. In order to link outcomes to use of the intervention we will assess perceived tailoring, and use of the intervention through web logging.

The background variables that are assessed include age, gender, education, income, alcohol use, and co-morbidity. Disease related symptoms like chest pain is assessed through WHO’s ROSE questionnaire [33]. Physical Activity is measured with the International Physical Activity Questionnaire IPAQ [34,35]. Stage of change is assessed with the scale URICA-E2 [36], which gives a more comprehensive assessment of stage than simply time before or after initiation of action. Self-efficacy is measured with modified versions of The perceived competence for regular physical exercise (PC-EX) scale [37]. Responses are given according to a scale from 0 (not at all) to 6 (to a great extent). We have previously used this scale with diabetes patients, and it performed satisfactorily with regards to both construct and predictive validity [29]. Regulatory focus is assessed with a short form of the Regulatory Focus Questionnaire [38]. This scale has been used successfully in the context of heart disease previously [39]. Social support is assessed with an adaptation of the scale from Barrera et al. [10]. Anxiety and Depression is assessed with Hospital Anxiety and Depression Scale (HADS) that is widely and successfully used for the post-discharge period that demonstrates satisfying diagnostic usefulness for screening depression symptoms and measuring anxiety of CVD patients [40]. We use the EQ-5D to measure health-related quality of life [41]. Perceived tailoring will be assessed *via* four items from Dijkstra [42]. eHealth literacy is assessed by the eHealth Literacy Scale [43].

Data on use of both interventions will be gathered through web logging. Number of log-ins, time logged in, what elements have been used most per user will be registered.

### Statistical analysis

As participants are randomized at group level, a multilevel analysis will be performed to check for clustering effects. If the intraclass correlation coefficients for our primary outcome variables are different from zero this will be taken into account in the following analyses, in order to reduce p-value bias. Potential confounders will be added as covariates. Data analysis will be performed using IBM SPSS and MLWiN. Group differences after intervention will be analysed with baseline data as a covariate in ANCOVA. Should clustering effects be found, multilevel mixed regression will be used.

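### Clustering is modelled only if an ICC check finds it, although whole monthly groups are randomised; with 16 to 17 groups the check often misses real clustering and the default ANCOVA then overstates precision

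*Protocol article*

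**What the plan says.** The Design section of the protocol article describes "randomizing the monthly clusters of participants to one of two conditions". Sample size estimation states "we need a total sample of 16 clusters with 15 participants each" and plans to recruit 17.

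The Statistical analysis section then sets out a sequence. First, "a multilevel analysis will be performed to check for clustering effects". Next comes the condition: "If the intraclass correlation coefficients for our primary outcome variables are different from zero this will be taken into account in the following analyses". The comparison itself is given as "Group differences after intervention will be analysed with baseline data as a covariate in ANCOVA", and the switch to another model as "Should clustering effects be found, multilevel mixed regression will be used".

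So ANCOVA is the default and the mixed model is the exception. The section names no test, level or threshold for deciding that an ICC differs from zero. Nothing elsewhere in the article commits to a cluster-adjusted analysis regardless of the check.

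**The concern.** The monthly group is the unit of randomisation, so the variance of the arm difference contains the between-group component by design. Leaving it out is justified only if that component is truly zero. A check that fails to find it among 16 or 17 groups is weak evidence of that.

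The article itself gives reasons to expect correlation within groups. On the shared stay it says "Since these people are hosted in the same environment for all of this period and social interaction related to the rehabilitation is encouraged". After discharge each group keeps a closed forum area with "discussions that are only accessible by those that are members in the same monthly group".

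At stake is the primary comparison of physical activity. If the check misses real clustering, the standard error is too small, the confidence interval too narrow and the false-positive rate above 5%. A reader of the trial report could not tell from a negative check whether this had happened. The main outcome is measured at 1, 3 and 12 months, so different time points could also end up with different models, each chosen from the trial's own data.

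**Working it through.** **Inputs from the protocol article.** 16 groups of 15, that is 16 × 15 = 240 participants; 17 groups to be recruited (Sample size estimation). Groups of 10–20 before consent and eligibility (Design). Alpha 0.05.

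**Assumed inputs.** The article gives no ICC, so I took 0, 0.01, 0.02, 0.05 and 0.10. Further assumptions are an 8:8 split (8:9 for 17 groups), equal group sizes, a normal outcome, no arm effect and two-sided tests. The baseline covariate is left out, so the ICC stands for the residual ICC after adjustment.

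**The plan's own figure.** The 240 cannot supply an ICC. For 15% against 5% with 80% power, a two-sided test needs 282 participants even at ICC 0. A one-sided test needs 222, and reaches 240 only with an ICC of about 0.006. The article states neither sidedness nor ICC. That is a separate matter, and nothing below depends on it.

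**Step 1: how far the ANCOVA standard error falls short.** With m per group, the true standard error exceeds the unadjusted one by about √(1 + (m − 1) × ICC). For m = 15:

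- ICC 0.01: √1.14 = 1.07
- ICC 0.02: √1.28 = 1.13
- ICC 0.05: √1.70 = 1.30
- ICC 0.10: √2.40 = 1.55

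**Step 2: type I error if clustering is ignored.** This is approximately 2 × [1 − Φ(1.96 / factor)], which gives 6.6%, 8.3%, 13.3% and 20.6%. Simulation (200,000 runs per setting) gives 6.6%, 8.4%, 13.5% and 20.8%.

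**Step 3: power of the ICC check.** Take the check as a between/within F test at 5% on 14 and 224 df, with critical value 1.736. The probability of detection is P(F > 1.736 × (1 − ICC) / (1 + 14 × ICC)). At ICC 0.05 the threshold is 1.736 × 0.95 / 1.70 = 0.970, giving 48%.

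**Step 4: the two-step rule.** If the check is significant, use a cluster-level t test on 14 df; otherwise use the unadjusted analysis.

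| Assumed ICC | Check detects | Falls back to ANCOVA | Error in fallback trials | Error of whole rule | Always cluster t test |
|---|---|---|---|---|---|
| 0 | 5% | 95% | 5.0% | 4.8% | 5.0% |
| 0.01 | 11% | 89% | 6.6% | 5.9% | 4.9% |
| 0.02 | 19% | 81% | 8.4% | 7.0% | 5.1% |
| 0.05 | 48% | 52% | 13.7% | 8.0% | 5.0% |
| 0.10 | 82% | 18% | 21.8% | 6.6% | 5.0% |

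**Step 5: sensitivity at ICC 0.01 / 0.02 / 0.05 / 0.10.**

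- 17 groups of 15: fallback 89% / 80% / 50% / 16%; whole-rule error 6.1% / 6.9% / 7.8% / 6.4%.
- 16 groups of 10: fallback 91% / 87% / 68% / 37%; whole-rule error 5.6% / 6.2% / 7.6% / 7.5%.
- Any positive ICC estimate triggers adjustment (16 groups of 15): fallback 41% / 30% / 11% / 2%; whole-rule error 4.0% / 4.5% / 4.9% / 5.0% with a t test, or 4.8% / 5.6% / 6.5% / 6.9% with a large-sample Wald test.

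**Step 6: reference distribution.** If the mixed model were tested against the normal distribution, 2 × P(t on 14 df > 1.96) = 7.0%. The article does not say which reference would be used.

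**The case against.** The plan is not blind to clustering: it names a multilevel model and gives limiting p-value bias as the reason. Five points can be made in its favour.

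- **The trigger is undefined.** If any positive ICC estimate leads to the mixed model, fallback is much rarer, and with a t test the error does not exceed 5%. This stands as a limit on size. The wording of the switch, that clustering effects be found, leans towards a significance test but does not settle it. An undefined trigger is itself a weakness, because it leaves the choice of model to be made after the data are seen.
- **The largest figures belong to one branch.** The 13.7% and 21.8% describe only trials that fall back, and at ICC 0.10 that is 18% of them. This stands; the error of the procedure as a whole is about 6–8%.
- **The inputs are assumed.** No ICC is given, the covariate is omitted, and 15 analysed per group may be high. This also stands. With 10 per group the error in fallback trials at ICC 0.05 drops to 10.5%, but fallback becomes more frequent and the overall error is little changed at 7.6%.
- **No Wald test is named.** Correct. The choice of degrees of freedom is a detail an article may leave to the analysis plan, so the 7.0% is a caution and not part of the defect.
- **The forum is not purely within-group.** Users can also post in discussions open to everyone. True, so the shared four-week stay is the stronger reason to expect correlation. Neither fact shows how large the ICC is.

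An analysis plan that is not shown could add detail, but that does not answer the point. The article states a rule, and the rule is what is wrong.

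**Conclusion.** The concern holds. In a cluster-randomised trial, allowance for the cluster cannot depend on a low-powered look at the same data, and the Statistical analysis section makes it do so.

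On the significance-test reading, with 16 groups of 15 and assumed ICCs of 0.01–0.05, about half to nine-tenths of trials would be analysed by an ANCOVA with a true error of 6.6–13.7%. Over assumed ICCs of 0.01–0.10 the full procedure errs 5.9–8.0% of the time against a nominal 5%. Inflation is nil if the true ICC is zero, and nil or smaller if any positive estimate triggers adjustment.

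That the rule is wrong is certain from the text. Its numerical effect depends on the assumed ICCs and on how the trigger is read. Because it bears on the validity of the primary test and costs almost nothing to correct, it should be changed before analysis.

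**What to change.** Remove the ICC check as a condition. State that every arm comparison, at each time point, uses a mixed model with a random effect for monthly group and the baseline value as covariate. Specify Satterthwaite or Kenward-Roger degrees of freedom, or alternatively a cluster-level t test on K − 2 df (14 for 16 groups, 15 for 17). Report the estimated ICC with its interval as a result, with no bearing on the choice of model.

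The cost is about one sentence in the analysis section, since a multilevel fit is already planned. If the true ICC is zero, intervals are slightly wider. With a t test on 14 df the critical value is 2.145, against 1.970 on 238 df, a ratio of 1.09, so about 9% wider.
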